### Outcomes evaluation

The evaluation of the BCP-VAMOS implementation process will be carried out based on RE-AIM (22) and CFIR (23). These frameworks enable to measure the quantitative and qualitative impact of an intervention on public health (26).

This study, despite focusing exclusively on the characteristics of the implementation, will describe the individual dimensions of RE-AIM (Reach = R and Effectiveness = E) to determine the impact of implementation and ongoing support on the program adaptation to the real world. The organizational dimensions (Adoption = A, Implementation = I, Maintenance = M) will be assessed to determine the factors involved in the implementation's success (see Table 2).

**Table 2 T2:** RE-AIM and CFIR information to evaluate the implementation of BCP-VAMOS, version 3.0. Brazil.

**RE-AIM, dimensions**	**RPT aims and outcomes measures**
^**a**^**Reach:** measure of participation in the intervention (individual level)	**Aim:** to describe the number, proportion, and representativeness of the participants in the intervention. **Quantitative:** recruitment, participation, and retention rates of participants calculated by PHC professional who will deliver the intervention. *Data collection:* registration of interested, enrolled, retained, and dropouts.
^**a**^**Effectiveness:** measure of the intervention's impact (individual level)	**Aim:** to show the results of the primary intervention outcomes. **Quantitative:** proportion of participants showing a behavior change in PA and EB by PHC professional. *Data collection:* baseline and post-intervention assessment.
**Adoption:** measure of the participation of location/teams interested in initiating the intervention (staff level)	**Aim:** to describe number, proportion, representativeness, and the characteristics of the location/PHC professionals who initiated the delivery of the intervention. **Quantitative:** adoption rate, demographic and social data of location/PHC professionals vs. the eligible ones. *Data collection:* electronic form filled out by PHC professionals. **Qualitative:** reasons that influenced the adoption and barriers to not adopt the intervention. *Data collection:* interview with PHC professionals.
**Implementation:** degree to which the intervention was delivered as intended	**Aim:** to evaluate the quality of the implementation, fidelity of delivery of the intervention, and the degree to which the strategies are implemented as intended. **Quantitative:** proportion of location/PHC professional that implemented the intervention as intended. *Data collection:* settings visit and process observation. **Qualitative:** protocol adaptations, barriers, and facilitators for implementation. *Data collection:* interview with managers, PHC professionals, and participants.
**Maintenance:** measure the extent to which the intervention is institutionalized (setting level)	**Aim:** to verify the continuity of the intervention by location/PHC professionals. **Quantitative:** number of new groups that have been implemented over time or after the delivery of the intervention by a PHC professional. **Qualitative:** reasons for implementing new groups or discontinuity. *Data collection:* interview with managers and PHC professionals.

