**Effectiveness**, assessed at the individual level, refers to the extent of the intervention's impact on the primary outcomes, how it changes behavior and affects the quality of life, and whether or not there are unintended results (positive or negative) (22). In this study, effectiveness will be assessed considering the primary outcomes of BCP-VAMOS: physical activity and eating behavior. Physical activity will be assessed through a self-report of the weekly practice (type, frequency, and duration) (34) and by accelerometry (35), which allows measuring the time spent on sedentary behavior, light, moderate, and vigorous physical activity. Eating behavior will be assessed through the habit and frequency of consumption of foods classified as healthy (fruits, greens, and raw or cooked vegetables) and unhealthy (sweets, snacks, and sugary drinks) (34). These data will be collected by the PHC professionals through a validated questionnaire for the BMC-VAMOS program (33). The effectiveness outcomes will be analyzed by PHC professional (staff level) to assess the impact of intervention strategies, comparing the IG to the CG.

**Adoption** is a measure at the organizational level of participation that refers to the representativeness of locations and/or agents who are willing to implement an intervention, considering those who are eligible (22). In this study, the number, proportion, and representativeness of local/PHC professionals who initiate the program delivery will be calculated using those certified by the online training with eligibility criteria. We will calculated the adoption rate by considering the ratio between the number of PHC professionals who initiated the implementation of the program in each UBS and the number of PHC professionals certified by the online training, multiplied by 100. To identify the factors that will influence the program adoption and non-adoption, qualitative data will be collected through interviews with PHC professionals.

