### Data analysis

Quantitative data will be expressed through descriptive analysis (absolute and relative frequency, mean and standard deviation) and inferential analysis to compare the impact of the intervention between the groups. To compare the characteristics between the groups, Fischer's exact and chi-square tests will be used. To verify the effect of the intervention, Student's paired t test or Wilcoxon test (continuous variables) and McNemar test (categorical variables) will be used. To compare changes between groups, Student's t test or Mann-Whitney *U*-test will be applied. The analyses will be performed using a 5% probability, and will be generated using the Statistical Package for the Social Sciences (SPSS)^®^ software, version 22.0. Qualitative data will be fully transcribed by a researcher, and their quality will be assessed by a second researcher. Through the technique of descriptive content analysis (38), the texts will be pre-analyzed (each interview will be read), coded (reduced to units of meaning consistent with the purpose of the study), and categorized (the participants' answers will be organized). The information will be coded deductively, following the conceptual model of the study and, if necessary, inductive codes will be added until saturation is achieved (39). The data will be double-coded in the QSR NVivo^®^ 12.0 software by two trained researchers. Intercoder reliability will be assessed employing Cohen's kappa (criterion> 0.80).

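### Table 2 makes effectiveness an undefined per-professional proportion changing, the outcomes are collected in finer detail, and the analysis section does not say which quantity is compared between arms

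*Protocol article*

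**What the plan says.** Three places in the protocol article bear on the between-arm effectiveness comparison.

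- **Outcomes evaluation, Table 2, Effectiveness row.** The only quantitative measure is the "proportion of participants showing a behavior change in PA and EB by PHC professional". Footnote a assigns this dimension, with Reach, to assessing impact in the two arms. The row gives no rule for when a participant has changed.
- **Outcomes evaluation, Effectiveness paragraph.** Physical activity is self-reported by type, frequency and duration, and is also measured by accelerometer, "which allows measuring the time spent on sedentary behavior, light, moderate, and vigorous physical activity". For diet, "Eating behavior will be assessed through the habit and frequency of consumption of foods classified as healthy" or unhealthy. On the unit of analysis: "The effectiveness outcomes will be analyzed by PHC professional (staff level) to assess the impact of intervention strategies, comparing the IG to the CG".
- **Data analysis.** For the within-group effect, "Student's paired t test or Wilcoxon test (continuous variables) and McNemar test (categorical variables) will be used". The next sentence gives Student's t test or Mann-Whitney for changes between groups and does not name the quantity.

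Study location and participants expects around 45 trained professionals and a minimum group of 8. The section headed New description randomizes facilities.

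**The concern.** Physical activity and eating behavior are the primary outcomes. If Table 2 governs, duration and accelerometer time are cut into changed or not changed and then averaged over a group that may hold only 8 people. In such a group the proportion moves in steps of 1/8 = 12.5 points, and gains of very different size on the same side of the cut count alike.

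The number of professionals is limited by how many complete the training, so precision lost here cannot easily be bought back with sample size. The open wording adds a second risk. With no cut-point and no named variable in the article, the choice between proportion and collected scale, and the choice of cut, could be made after the data are seen.

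**Working it through.** **The plan's own figure.** 45 professionals × 8 participants = 360, as stated. This is a feasibility count. There is no stated power to reproduce.

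**Inputs from the article.** 45 professionals, 8 participants each, 5% level, analysis by professional.

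**Assumptions, not in the article.** Two-sided test, 22 v 23 professionals, no dropout, professionals independent, normal change scores with SD 1, standardized difference d = 0.2 to 0.5, intracluster correlation (ICC) ρ = 0.01 to 0.10, and 50%, 30% or 20% of control participants above the cut.

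**Formulas.** Both analyses are t tests on one summary per professional (43 df).

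- Mean change: V = ρ + (1 − ρ)/8; SE = √[V(1/22 + 1/23)]; noncentrality d/SE.
- Proportion: p_I = Φ(Φ⁻¹(p_C) + d). In each arm V = p(1 − p)[ρ_b + (1 − ρ_b)/8], where ρ_b is the ICC of the yes/no variable implied by ρ. At a median cut ρ_b = (2/π)·arcsin(ρ). Noncentrality is (p_I − p_C)/√(V_C/22 + V_I/23).

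**Worked case: ρ = 0.05, d = 0.3, p_C = 50%.**

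- Mean: V = 0.05 + 0.95/8 = 0.16875; SE = 0.1225; 0.3/0.1225 = 2.449; power 67%.
- Proportion: p_I = Φ(0.3) = 0.618. V_C = 0.25 × (0.0318 + 0.9682/8) = 0.0382. V_I = 0.236 × (0.0309 + 0.9691/8) = 0.0359. SE = √(0.0382/22 + 0.0359/23) = 0.0574; 0.118/0.0574 = 2.05; power 52%.
- Ratio of information: (2.05/2.449)² = 0.70. Using the proportion is like running the mean comparison with about 0.70 × 45 ≈ 32 professionals.

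**Grid.** Power in %, mean change v proportion at p_C = 50/30/20%:

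| ICC | d = 0.2 | d = 0.3 | d = 0.4 | d = 0.5 |
|---|---|---|---|---|
| 0.01 | 43 v 30/29/26 | 77 v 58/57/52 | 95 v 82/82/77 | 99 v 95/95/93 |
| 0.05 | 36 v 27/26/23 | 67 v 52/51/46 | 89 v 76/76/71 | 98 v 92/92/89 |
| 0.10 | 30 v 23/23/21 | 57 v 46/44/41 | 81 v 69/69/65 | 95 v 87/87/84 |

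The loss runs from about 4 points (ICC 0.01, d = 0.5) to about 25 (ICC 0.01, d = 0.3, 20% of controls changing). Simulation of the same design agrees: at ICC 0.05 and a median cut it gives 67% v 52%, 89% v 76% and 98% v 92% for d = 0.3, 0.4 and 0.5. Outside the grid, simulation gives about 1 to 10 points at d = 0.1 or 0.6, and up to about 34 if only 10% of controls change.

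**Fewer units.** Facilities are randomized, so there may be fewer than 45 independent units. With 23 units the simulated loss is about 2 to 25 points.

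**Distribution and cut-point.** Simulated at ICC 0.05, d = 0.3:

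- Cut at the control median: normal residuals 66% (mean) v 51% (proportion); Laplace 66% v 72%; t with 3 df 68% v 75%. With heavy tails the proportion does as well or better.
- Cut 1 SD above the control mean: over d = 0.3 to 0.5 the proportion loses about 8 to 30 points under every distribution tried.

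**Gain from baseline adjustment.** With baseline-to-9-month correlation r (not in the article), residual variance is (1 − r²)σ² for the adjusted value and 2(1 − r)σ² for an unadjusted change. The ratio is (1 + r)/2, for example 0.65, 0.75 and 0.85 at r = 0.3, 0.5 and 0.7. At participant level, therefore, adjustment is at least as precise as an unadjusted change score.

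**The case against.** The strongest case on the other side has four parts.

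1. **The analysis section may already keep the collected scale.** Its between-arm test for changes is a t or rank test, and the two-sample categorical tests are reserved for comparing group characteristics. The Effectiveness paragraph also speaks of outcomes, not of a proportion. This stands in part. A reader might infer from Table 2 that the plan has discarded the continuous data, and the text does not go that far. But a t test or Mann-Whitney runs equally well on per-professional proportions, and Table 2 and the Effectiveness paragraph share that unit. The ambiguity therefore remains.
2. **Table 2 is a RE-AIM summary.** It lists rates, proportions or counts for every dimension, and a condensed article may leave the definition of a change to a fuller plan. The missing cut-point alone would not be a finding. What the article does fix is a proportion as the only quantitative effectiveness measure, with a footnote giving that dimension the between-arm role, next to text pointing elsewhere.
3. **The power loss is not a property of this plan.** This stands. The loss rests on assumed inputs, and even its sign depends on the distribution and the cut.
4. **Eating frequency may be ordinal.** This also stands. The normal-model figures apply mainly to physical activity.

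**Conclusion.** The point holds as an inconsistency with a conditional cost. Table 2 names an undefined proportion, the Effectiveness paragraph collects finer measures, and the Data analysis section does not say which of them is compared.

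If the proportion decides, the loss is roughly 4 to 25 points of power. This assumes normal change, about 45 independent professionals with 8 participants each, d = 0.2 to 0.5, ICC 0.01 to 0.10, and 20% to 50% of controls changing. It can vanish or reverse for heavy-tailed change cut near the median, and it is consistently present for a cut well above the control mean.

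A reader might take a fixed loss of 5 to 20 or more points as established for this trial. The document does not support that, because it states no effect size, SD, ICC, cut-point or power. The recommendation does not depend on the exact size: it removes the ambiguity, and baseline adjustment also improves on an unadjusted comparison of changes.

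**What to change.** Reconcile Table 2, the Effectiveness paragraph and the Data analysis section as follows.

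- Make the between-arm effectiveness measure the 9-month value of each outcome on its collected scale, for example accelerometer minutes by intensity, adjusted for its baseline value and with facility as the cluster.
- Provide a transformation or rank-based analysis if activity data are skewed or heavy-tailed, and an ordinal method for eating frequency if its response scale requires one.
- Keep the proportion changing as a supporting descriptive RE-AIM figure, with its definition and cut-point written down before the data are examined.

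The cost is wording only, since the baseline and post-intervention measurements are already planned. The downside is that a mean difference is slightly less simple to communicate to policy-makers than a percentage. Reporting the percentage alongside it largely meets that.

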**CFIR, domains**
**Intervention characteristics:** main attributes that influence the success of the intervention	**Aim:** to describe the characteristics that influence the successful implementation of the intervention. **Qualitative:** adaptability, complexity of implementation, barriers, and facilitators. *Data collection:* interview with managers, PHC professionals, and participants.
**Outer setting**: external factors of the organization can have positive or negative influences on the implementation of the intervention	**Aim:** to identify external factors that may influence the successful implementation of the intervention. **Qualitative:** perception of the patient's needs and resources for implementation. *Data collection:* interview with managers and PHC professionals.
**Inner setting**: aspects of the organization's functioning and structure that influence the success of the intervention	**Aim:** to describe the internal characteristics of the organization. **Qualitative:** climate and readiness of location/PHC professionals for implementation of the intervention. *Data collection:* interview with managers and PHC professionals.
**Characteristics of individuals**: level of knowledge, belief, attitude, and engagement of providers during implementation that may determine the success of the intervention	**Aim:** to identify personal characteristics that may influence the implementation of the intervention. **Qualitative:** knowledge and beliefs, self-efficacy, identification with the organization, and other personal attributes. *Data collection:* interview with PHC professionals.
**Process:** decision making of the organization's agents that influence the success of the intervention	**Aim:** to assess the organization's commitment to the intervention protocol. **Qualitative:** involvement of location/PHC professionals who led the intervention, barriers, and facilitators for implementation. *Data collection:* monitoring the stages and interviewing managers, PHC professionals, and participants.

PRCT, pragmatic randomized controlled trial; PA, physical activity; EB, eating behavior. ^a^These RE-AIM will be used to assess the impact of the implementation on the intervention group and control group, whose data will be collected by the PHC professionals (providers) of the intervention.

**Reach** is a measure at the individual level of participation, which refers to the characteristics and percentages of the target population's participation in the intervention (22). In this study, reach will be assessed as the number, proportion, and representativeness of program recipients enrolled and retained in the program. We will assess the involvement of program recipients based on three reach rates: recruitment (ratio between the number of users interested in participating in the program in relation to the number of exposed users—users served at the UBS during the period when the program was announced, multiplied by 100); participation (ratio between the number of participants who will start the program in relation to the number of eligible participants in the program, multiplied by 100); retention (ratio between the number of participants who will complete and the number of participants who started the program, multiplied by 100). These reach rates will be calculated by PHC professional, comparing the IG to the CG.

To reach the participants (recruitment), we will make available printed materials (posters, folders) and we will suggest the use of social networks, in addition to the media (radio, television, internet) to publicize the program. We recommend employing these strategies during the 30-day period prior to the start of the program. In order to recruit participants, we will establish the following eligibility criteria: being 18 years of age or older, being registered and having been attended at UBS in the 30 days prior to the start of the program (30 days from the disclosure), not meeting the minimum recommendations of PA practice (150 min per week of moderate and/or vigorous PA) and/or having inappropriate eating behavior and/or being overweight/obese and/or non-communicable chronic diseases. We will provide a questionnaire (33) and guidelines (https://vamos.ufsc.br/orientacoes-para-questionario-vamos/) to PHC professionals to screen participants. This screening will be carried out through a meeting scheduled prior to the start of the program with interested users. At this meeting, in addition to screening assessments, PHC professionals will be recommended to clarify the objectives and methodology of the program. In addition, we will assess the reasons for participants' absences and dropouts throughout the program. For this, we use the PHC professionals' monitoring records (attendance list and replacement of the sections), which will be guided to record the date and reason for the termination of each participant.

**Effectiveness**, assessed at the individual level, refers to the extent of the intervention's impact on the primary outcomes, how it changes behavior and affects the quality of life, and whether or not there are unintended results (positive or negative) (22). In this study, effectiveness will be assessed considering the primary outcomes of BCP-VAMOS: physical activity and eating behavior. Physical activity will be assessed through a self-report of the weekly practice (type, frequency, and duration) (34) and by accelerometry (35), which allows measuring the time spent on sedentary behavior, light, moderate, and vigorous physical activity. Eating behavior will be assessed through the habit and frequency of consumption of foods classified as healthy (fruits, greens, and raw or cooked vegetables) and unhealthy (sweets, snacks, and sugary drinks) (34). These data will be collected by the PHC professionals through a validated questionnaire for the BMC-VAMOS program (33). The effectiveness outcomes will be analyzed by PHC professional (staff level) to assess the impact of intervention strategies, comparing the IG to the CG.

**Adoption** is a measure at the organizational level of participation that refers to the representativeness of locations and/or agents who are willing to implement an intervention, considering those who are eligible (22). In this study, the number, proportion, and representativeness of local/PHC professionals who initiate the program delivery will be calculated using those certified by the online training with eligibility criteria. We will calculated the adoption rate by considering the ratio between the number of PHC professionals who initiated the implementation of the program in each UBS and the number of PHC professionals certified by the online training, multiplied by 100. To identify the factors that will influence the program adoption and non-adoption, qualitative data will be collected through interviews with PHC professionals.

**Implementation** at the organizational level refers to the degree to which delivery agents comply with several elements of an intervention protocol (22). In this study, the quality of the BCP-VAMOS implementation will be assessed based on strategies for recruiting, retaining, and monitoring participants. This analysis will be performed by PHC professional, comparing the IG to the CG. During a 1-year follow-up, a detailed manual will be developed, containing all the implemented strategies and the approximate dates for the completion of each intervention component. The manual will help in the development of checklists to assess the fidelity of the intervention delivery and the degree to which strategies are implemented as intended. A trained researcher will visit the intervention sites to observe and complete the checklist, in addition to conducting interviews with PHC professionals.

**Maintenance** at the organizational level assesses the extent to which an intervention becomes institutionalized or part of routine practices and organizational policies (22). In this study, the assessment of maintenance aims to show if new groups will be delivered during the implementation process of the BCP-VAMOS or if the local organization is interested in institutionalizing the program. This evaluation will be carried out shortly after the last section of the program, through an interview with PHC professionals and managers.

The CFIR pragmatic framework (23), widely used in implementation research in the health area (36), will be used to qualify the outcomes measures. CFIR describes 37 implementation constructs, categorized into five domains: innovation/intervention characteristics, outer setting, inner setting, characteristics of the individuals involved, and process of implementation (23).

**Innovation characteristics** directly influence the success of the implementation (36). The constructs evaluated in this domain are related to information about the *source of the intervention, quality of evidence, organizational advantage, adaptability, trialability, complexity, design and presentation of the intervention, and costs* (23). In this study, we are especially interested in adaptability—the degree to which the intervention can be customized or refined to meet local needs.

Increasingly recognized as an active part of implementation, the **outer setting** domain is composed of constructs that address *patient needs and resources, cosmopolitanism, peer pressure, external policies, and incentives* (23). Health systems are hierarchically organized and interconnected. Changes in the external environment can influence, positively or negatively, implementation (23). Identifying these factors in this study may help other organizations to replicate implementation successfully.

The **inner setting** at the organizational level describes constructs that relate *structural characteristics, networks and communications, culture, implementation climate, and readiness for implementation*. These aspects are interrelated and influence implementation (23). In this study, we will evaluate the quality of internal communication, adaptability in decision-making, receptivity of the individuals involved, and organizational commitment to intervention.

Organizations are composed of individuals and their behaviors. Little is known about the interaction between individuals and their propagating effects through teams and organizations in implementation (36). The domain regarding **characteristics of individuals** lists constructs that can reveal *knowledge and beliefs of the professionals involved, self-efficacy for implementation, personal stage of change, identification with the organization*, and *other personal attributes and values* (23). All these items can influence the degree of commitment to service innovation and affect the implementation of an intervention (36). Trying to understand these influences is part of this study, as they can further qualify the health professionals' training for the implementation of the program on future occasions.

**Process** is the domain that represents the greatest challenge during program evaluations in public health (23, 36). It is evaluated through the constructs of *planning, engagement, execution*, and *reflection, and evaluation of the professionals involved in delivering the intervention*. The better each of these four mechanisms is implemented, the better and more effective the implementation will be (23). Thus, in this study, all items will be evaluated.

CFIR will be used to gather information about the constructs that affect the implementation of the innovation. It will also aid in the identification of the contextual determinants (barriers and facilitators) that can be used to guide the selection of the most appropriate strategies for the success of the intervention (see Table 2). These data will be collected through interviews based on the CFIR matrix (www.cfirguide.org). From the perception of PHC professionals, managers and participants of the PMC-VAMOS, we will classify and code the barriers and facilitators within each of the domains and constructs of the CFIR.

